#### Surveys

The baseline survey was designed to assess usual use of food parenting practices as well as additional parental, household, and environmental factors of interest. Participants completed the same survey at each time point (T1-T4). This survey was administered on the web via REDCap (Research Electronic Data Capture; Vanderbilt University), a secure, web-based data collection platform sponsored by the University of Minnesota and provided by the Clinical Translational Research Institute [39]. Participants took an average of 30 to 45 minutes to complete the survey. To enhance engagement, we incorporated visual elements within REDCap, including our Preschool Plates cohort study logo, motivational messages (eg, “Over Halfway Done! Keep it Up!”), and a progress bar to help participants track their completion status.

In the survey, food parenting practices were assessed using subscales from the following 4 questionnaires: Comprehensive Feeding Practices Questionnaire [33], Food Parenting Inventory [34], Structure and Control in Parent Feeding [35], and Parenting around Snacking Questionnaire [36]. In addition, covariates and effect modifiers of interest at the child level (eg, developmental stage [37], temperament [38], mood [39], and hours spent in day care), parent level (eg, parenting style [42] and mental health [43]), family level (eg, acculturation [54] and food insecurity [44,45]), child-level demographics (eg, age, race or ethnicity), parent-level demographics (eg, educational attainment and employment status), and family-level demographics (eg, public assistance, income, and socioeconomic status) were assessed via this survey.

#### 24-Hour Dietary Recalls

Interviewer-led 24-hour dietary recalls were used to assess the quality and quantity of child dietary intake. Three 24-hour dietary recalls were collected for each child participant at baseline (T1) and each follow-up period (T2-T4). General availability to complete recalls was gathered for each participant individually by data collectors during their in-person visit. Participants had the ability to provide their availability for every day of the week, including weekends. Participants were given an 8-day window to complete their recalls, with a hard stop 14 days after their start date. The date and time for recalls were random but based on participants’ provided availability. Recalls were completed by a team of trained and certified staff based out of the Nutrition Coordinating Center using the Data System for Research [55].

A multiple-pass interview technique was used to prompt for a complete food and beverage recall and descriptions. Because preschool-aged children were not considered reliable reporters of dietary intake, recalls were conducted with the index child’s enrolled parent using protocols developed and validated by the Nutrition Coordinating Center for the collection of data on the dietary intake of young children [52]. Parents were provided with multiple resources to assist with dietary intake reporting, including the Food Amounts Booklet (designed for use with young children) to help estimate portion sizes. To reduce missing data and minimize bias from parental assumptions about foods consumed in their absence, we also provided the Foods Fed by Other Adults handout, which could be completed by individuals such as day care providers when the enrolled parent was not present.

Intake for the 3 recalls was averaged across days to create mean scores for intake of food categories of interest (eg, fruits, vegetables, sugary beverages, and salty and sweet snacks). Furthermore, HEI-2022 [32] total and component (eg, added sugars and sodium) scores will be calculated at each data collection time point (T1-T4) using methods designed for estimating overall dietary quality for an individual within an etiologic study, specifically the multivariate Markov chain Monte Carlo approach [56,57]. HEI is a scoring system that was developed to measure the degree to which a diet is consistent with the Dietary Guidelines for Americans and is a valid and reliable measure of diet quality [58]. The closer an HEI score is to 100 (range 0-100), the more aligned it is with the Dietary Guidelines for Americans [58,59]. The HEI-2022 total score is the sum of 13 subcomponent scores that measure adequacy (total fruits, whole fruits, total vegetables, greens and beans, whole grains, dairy, total protein foods, seafood and plant proteins, and fatty acids) and moderation (refined grains, sodium, added sugars, and saturated fats) [32]. This measure of overall dietary quality will help us to understand the longitudinal impact of specific patterns of food parenting on the child’s overall diet quality over time (at 6-month intervals for 2 years; refer to hypothesis 4 in the Results section).

#### Anthropometric Measurements

At the T1, T3, and T4 data collection visits, child participants’ height and weight were measured by trained study staff following a standardized protocol. For each visit, children were measured using a calibrated digital scale (to the nearest 0.1 kg) and a stadiometer (to the nearest 0.1 cm). Two measurements of height and weight were taken, and if the values differed by >0.5 units, a third measurement was collected. The final recorded values were determined by averaging the 2 closest measurements. All data collectors underwent training on proper measurement techniques, including instructions on positioning the child, ensuring minimal clothing, and verifying equipment calibration [53,54]. Data collectors underwent retraining every quarter. A measurement log was maintained within REDCap to record each measurement and any procedural notes.

In the event a family could not attend the on-campus visit for anthropometric measurements, parent consent was obtained to access the child’s medical records from the MHealth Fairview health system. Children whose data were extracted from electronic health records were required to have seen a health care practitioner within the preceding 6 months.

### Retention Efforts

Retention strategies focused on consistent communication to ensure participant engagement and adherence. Participants received regular reminders to complete EMA, dietary recalls, and surveys. Study staff and data collectors were trained to follow up with participants promptly, typically within 1 business day, to address any questions, delays, or noncompliance.

Participants scheduled for in-person visits were contacted via text or phone calls to confirm the date, time, and location. Confirmation emails provided detailed logistical information, including GPS coordinates, parking instructions with photos, and other relevant details. Reminder texts were sent the day before visits to reinforce appointment schedules and logistical information.

Postcards were sent at multiple time points to maintain participant engagement and provide reminders for study activities. Mother’s Day and Father’s Day postcards were sent to all enrolled participants. Annual birthday postcards were mailed to parents and children during the study period. In addition, participants were sent a postcard reminder 2 weeks before remote data collection windows (T2) and 1 week before in-person visits (T3 and T4).

Participants returning for in-person visits at T3 received personalized coloring books created by study staff. This coloring book was tailored to the study’s preschool-age population and was designed to encourage participant involvement in follow-up visits.

### Incentives

Participants were compensated for their time and effort across the 5 data collection periods, with a maximum potential compensation of US $950 over the 2-year study period. At the baseline visit (T1), participants were provided with a Greenphire ClinCard, a reloadable payment card, which was used to distribute incentives throughout the study. Compensation was structured to reflect the time and effort required for specific study components. Surveys were completed at each time point (T1-T4) and were incentivized with US $50. For each set of three 24-hour dietary recalls, participants received US $25 per recall, totaling US $75 per data collection point. Completion of the 8-day EMA protocol was compensated with US $75 per time point. For anthropometric measurements collected in person at T1, T3, and T4, participants received US $50 per visit. If anthropometric data were collected from medical records rather than in person, no payment was provided for that time point’s measurement. This incentive structure was designed to equitably compensate participants while encouraging engagement and retention throughout the study.

### Pilot Study

Kids EAT! was a National Institutes of Health–funded K23 study (principal investigator: [name]), which used mixed methods (interviews, surveys, and EMA) to explore the real-time use of food parenting practices within a racially, ethnically, and socioeconomically diverse sample of parents of preschool-aged children (n=120) [15,20,60,61]. EMA protocols for Kids EAT! included asking parents to respond to a series of signal- and event-contingent prompts delivered to their smartphones. Results from Kids EAT! demonstrated feasibility in using EMA with parents from diverse backgrounds and collecting data from parents working shift work, during time periods when children were in school or day care, and from parents with differing levels of comfort with technology. The Preschool Plates cohort study protocol used the successful staff training models, data collection protocols, and participant incentive plans used in the Kids EAT! study. Kids EAT! parent participants were successfully engaged in several different data collection approaches similar to those proposed in this study, including web-based surveys and EMA.

### Statistical Analysis Plan

#### Overview

R (R Foundation for Statistical Computing) will be used for data cleaning and main analyses. Distributions of key outcome variables will be assessed and transformed if necessary. Unless otherwise specified, hypothesis tests will be conducted using a 2-sided α level of .05.

EMA responses will be aggregated to derive scores for each of the 4 food parenting practice domains during each data collection period. Given the unequal number of questions related to each domain, 2 versions of domain scores will be created by computing (1) the number of items endorsed in each domain and (2) the proportion of items endorsed in each domain. Domain scores will be calculated for responses given at each event prompt (typically 2-8 per day over each 8-day data collection period).

Food parenting practice domain scores will be aggregated and compared visually and statistically at the event level (eg, breakfast, lunch, snack, and dinner) and by time period (eg, 9 AM to noon, 3 PM-5 PM, and 5 PM-9 PM). In addition, for each data collection period, we will fit linear mixed models for each domain of the form (M1) *D_ij_ = β_0_ + β_1_Z_ij_ + β_2_X_i_ + b_i_ + ε_ij_*, where *D_ij_* is the domain score for person *i* at event prompt *j*, *Z_ij_* is the event characteristic of interest (meal or time period indicator), *X_i_* is a set of baseline characteristics for person *i*, *b_i_* is a person-specific random effect, and *ε_ij_* is the residual. Longitudinal response patterns in domain scores will be visualized and qualitatively compared. We will calculate each individual’s SD, IQR, and entropy of domain scores across their longitudinal observations. How between-day fluctuations in food parenting differ across individuals will be quantified using longitudinal mixed models, similar to those described above, with the event characteristics *Z_ij_* representing between-day factors such as day of the week. The SD, IQR, and entropy of residuals from these models will also be summarized to characterize between-day fluctuations.

The distribution of the summary measures (SD, IQR, and entropy) of the longitudinal models described above will be used to derive measures of the consistency and endurance of food parenting practices. A metric of within-day consistency across event characteristics (eg, meal type) will be derived by calculating the distribution of SDs of individual residuals from model (M1) and then calculating an individual’s *z* score relative to this distribution. For example, an individual whose food parenting practices fluctuate substantially across meals will have a large SD of residuals relative to the population, so their *z* score will be relatively large. Consistency *z* scores will be used as predictors of child dietary intake in aim 2. Endurance will be measured by applying a similar *z* score approach but with models that incorporate data across multiple data collection periods. For example, model (M1) will be expanded to include data from times T2 to T4, and endurance *z* scores will be calculated from the distribution of spread summary measures (SD, IQR, and entropy) of the residuals from this expanded model.

Individual food parenting practice domain scores, as well as consistency and endurance metrics, will be used as inputs to a k-means algorithm (implemented using the *kmeans* package in R) to identify clusters of parents observed to use similar food parenting practices over the data collection period. For example, this technique might distinguish subsets of individuals who consistently and primarily use structure and autonomy support practices and those who use these practices less consistently or more commonly use coercive and indulgent practices. We will apply the k-means algorithm with a modest number of clusters (3-5) to ensure that the resulting groups are of sufficient size to accurately characterize them. Descriptive statistics will be used to summarize and compare the food parenting practices as well as demographic and family characteristics of each cluster. Cluster stability metrics and qualitative assessment of the scientific meaningfulness of the clusters will be used to choose a final number of clusters that will define subgroups for inclusion in the following analyses.

To examine the longitudinal impact of within- and between-day fluctuations in food parenting practices on child dietary intake, we will fit regression models for the outcome of child HEI measured from 24-hour dietary recall at time points T2 to T4. The main predictors of interest will be the individual-level summary measures of the 4 food parenting practice domains derived above. Our primary models will include the subgroup indicators classifying parents according to food parenting practice patterns, but we will also consider models that use average domain scores as well as consistency and endurance metrics. We will fit separate linear regressions for each data collection period, as well as longitudinal models that incorporate data across the time points T2 to T4. For period-specific models, we will include cluster indicators as well as consistency *z* scores that reflect the degree of within- and between-day fluctuations in food parenting practices during that period, along with relevant adjustment covariates. For longitudinal models, we will also include endurance *z* scores that reflect whether food parenting practices are maintained across data collection periods.

To identify momentary predictors of within- and- between-day fluctuations in the use of food parenting practices across time and context, we will combine the signal and event EMA survey data to understand how momentary factors (eg, mood, stress, and time constraints) affect food parenting practices. The main statistical approach will be to fit longitudinal linear mixed models of the form: (M2) *D_ij_* = *β_0_* + *β_1_W_ij_* + *β_2_X_i_* + *b_i_* + *ε_ij_*. Here, *W_ij_* represents a *vector* of momentary predictors, which will be derived by summarizing signal surveys within fixed time windows before the event *j*. Initially, we will define 

, with the superscript in parentheses indicating the number of hours before the event covered by that variable. For instance, 

 could reflect the average level of stress reported from signal surveys responded to in the 3 hours preceding the given event survey. We will fit separate models for each domain score during each data collection period; to increase power, we will also fit combined models that incorporate responses across multiple data collection periods. Single-predictor models (involving 1 type of momentary predictor, eg, stress) as well as multipredictor models will be considered. Time windows will be adjusted based on the observed response patterns of data, and if the momentary predictor data are overly sparse, multiple imputation will be used to fill in missing *W*values. In exploratory analyses, we will investigate whether momentary predictors interact with each other or with fixed and summarized individual characteristics (ie, consistency and endurance *z* scores) to impact food parenting practices. This will allow us to explore whether the strength of associations between momentary predictors and food parenting practices varies based on individuals’ levels of volatility in these practices.

Some participants may respond sporadically to event prompts, resulting in gaps between event prompt responses, which make it difficult to assess longitudinal patterns. We will begin by characterizing missing data patterns by participant and temporal factors, including the end-of-day prompts asking participants to indicate why they did not respond to prompts on a given day. Then, we will define and analyze a subset of “regularly responding” individuals for which there is sufficient data to characterize between-day fluctuations in food parenting practices, for example, a subset of individuals who have at most 2 days of event prompt nonresponse during their data collection period. To explore overall patterns and associations with non-EMA outcomes, we will augment this regularly responding set with data from individuals with more sporadic response patterns but who, based on their responses to end-of-day prompts, more plausibly have responses missing at random (eg, reported “forgot” rather than “too stressed”).

Food parenting practices and their associations with other measures may vary across subgroups defined by, for example, child developmental stage and parent cultural background. While our power to formally test for effect heterogeneity across these subgroups is limited, we will describe these differences by including interaction terms for these subgroups in the regression models described above.

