## Results

### Overview

Recruitment and data collection began in October 2023. At the time of this protocol paper’s submission, data collection is still in progress and is expected to continue through November 2026. A racially and ethnically diverse cohort was successfully enrolled, with 28.3% (72/254) of enrolled participants identifying as White and 71.7% (182/254) identifying as Black, Indigenous, or people of color. Refer to Table 2 for detailed information on the characteristics of the Preschool Plates baseline sample.

Hypotheses

This study hypothesized the following:

Use of food parenting practices will vary within- and between-days; unique patterns will emerge across time (eg, time of day and day of week) and context (eg, location and type of eating occasion).Distinct patterns in food parenting approaches will emerge; distinct pattern features will include mean levels of engagement in specific food parenting practices (by domain), as well as consistency in approach across day-, week-, and 6-month intervals, and endurance (or lack thereof) of patterns across time.Healthful eating occasion–level dietary quality (ie, Healthfulness of Meal Index assessed via EMA) will be positively associated with supportive feeding practices (eg, structure and autonomy support) and inversely associated with unsupportive practices (eg, coercive control and indulgent).Consistent and enduring use of supportive feeding practices will be associated with a more healthful overall diet quality (ie, HEI assessed via 24-hour dietary recalls) cross-sectionally and at 2-year follow-up, as compared to inconsistent or short-lived use of supportive practices and consistent and enduring use of unsupportive practices.We expect to identify numerous momentary predictors of significance (eg, mood, stress, child behavior, and time constraints). Parents will shift within the day from supportive feeding practices toward unsupportive feeding practices in response to momentary predictors (eg, high stress, low mood, or limited time).

**Table 2 table2:** Characteristics of the Preschool Plates baseline sample (N=254).

Characteristics		Values
Child age (y), mean (SD)		3.48 (0.59)

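### Day-of-week inference from a model whose only random effect is the parent treats meals on one day as independent replicates, so it is likely anticonservative by an amount the plan does not fix

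*Protocol article*

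**What the plan says.** All of this is in the protocol article. Under Statistical Analysis Plan, Overview, M1 is written out in full: D_ij "is the domain score for person" i at event prompt j, Z_ij is a meal or time-period indicator, X_i are baseline characteristics, b_i "is a person-specific random effect", and the last term is a residual. Event reports are "typically 2-8 per day over each 8-day data collection period".

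Between-day variation is then to be quantified with "longitudinal mixed models, similar to those described above, with the event characteristics" Z_ij now "representing between-day factors such as day of the week". The section states no parent-day term, serial correlation or robust variance. Residuals from these models are also summarised by SD, IQR and entropy, to describe between-day fluctuation.

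Unless otherwise specified, "hypothesis tests will be conducted using a 2-sided α level of .05". Hypothesis 1, in the Results section, expects that "unique patterns will emerge across time (eg, time of day and day of week") and across context.

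**The concern.** A factor that is constant within a day is replicated by days, not by meals. Each parent gives about 8 days per collection period, and all parents start on the same weekday. Over eight consecutive days, six of the seven weekdays occur once per parent. Nearly all of a parent's reports for a given weekday then share one calendar day and whatever happened on it, such as a sick child or a stressful day. If such events shift the whole day, the residuals of that day's meals are correlated. M1 still judges the weekday contrast against event-level error.

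This does not require parents to differ in their weekday pattern; it arises even if all share the same one. What is at stake is the day-of-week part of hypothesis 1. Chance differences between days could be reported as weekday patterns, and intervals for weekday differences could be too narrow.

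**Working it through.** **Inputs from the protocol article**
- Two-sided alpha 0.05; one parent random effect; event-level score (Statistical Analysis Plan, Overview).
- Reports per day, m: typically 2 to 8 (same section). A complete day needs at least 2 event reports (Ecological Momentary Assessment).
- 8 days per period (Ecological Momentary Assessment) and 200 families (Power Analysis).
- The Power Analysis counts 4 responses a day, but as event or signal responses. Domain scores come from event prompts, so m = 4 is used only as one value within 2 to 8.

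**Assumed, because the article gives no figure**
- rho, the share of within-parent variance that lies at parent-day level: 0.05 to 0.30.

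**Formulas**
- Variance understatement for a day-level contrast: deff = 1 + (m − 1)·rho.
- 6-df test: actual size = P(chi-square with 6 df > 12.59/deff).
- 1-df contrast (for example weekend against weekday): actual size = 2·[1 − Φ(1.96/√deff)].

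**The plan's own figure.** At rho = 0, deff = 1 and both formulas return 5%.

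**Example.** With m = 4 and rho = 0.10, deff = 1 + 3 × 0.10 = 1.30. Then 12.59/1.30 = 9.68 gives 13.9%, and 1.96/√1.30 = 1.72 gives 8.6%.

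| m | rho | deff | 6-df size | 1-df size |
|---|---|---|---|---|
| 2 | 0.05 | 1.05 | 6.2% | 5.6% |
| 2 | 0.10 | 1.10 | 7.6% | 6.2% |
| 2 | 0.20 | 1.20 | 10.5% | 7.4% |
| 2 | 0.30 | 1.30 | 13.9% | 8.6% |
| 4 | 0.05 | 1.15 | 9.0% | 6.8% |
| 4 | 0.10 | 1.30 | 13.9% | 8.6% |
| 4 | 0.20 | 1.60 | 24.8% | 12.1% |
| 4 | 0.30 | 1.90 | 35.7% | 15.5% |

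**Simulation check.** 200 parents, 8 days, no true weekday effect, 600 runs per setting (Monte Carlo standard error about 1 to 2 percentage points). A within-parent estimator stood in for the parent random intercept. With m = 4 the 6-df test rejected in 5.5% of runs at rho = 0, and in 8.5%, 15.7%, 25.8% and 39.2% at rho = 0.05, 0.10, 0.20 and 0.30. With m varying from 2 to 8, the last four figures were 10.2%, 20.5%, 41.7% and 53.5%. With a parent-day variance component added (rho taken as known), rejection was 4.0 to 6.2% in every setting.

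**Check in the other direction.** Stable parent-by-meal-slot differences were added to the data but left out of the model (m = 4). Their variance is expressed relative to the rest of the within-parent variance. 6-df rejection:

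| Omitted parent-by-meal variance | rho = 0 | 0.05 | 0.10 | 0.20 |
|---|---|---|---|---|
| 0.10 | 3.7% | 4.7% | 12.7% | 22.3% |
| 0.25 | 2.0% | 4.8% | 7.5% | 14.8% |
| 0.50 | 0.5% | 3.0% | 4.8% | 9.5% |

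The omitted variance enlarges the event-level error without adding to the day contrast, so the test can become conservative.

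**The case against.** Four points can be made for the plan.

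1. **The correlation is unknown.** A reader might infer from the model form that day-of-week tests reject far more often than 5%. The article does not support that, because it gives no within-day correlation after the parent effect is removed. With 2 reports a day and rho = 0.05 the 6-df size is 6.2%, and the 1-df size at 2 reports stays at or below 8.6% over the whole range. A reader might also infer that the test is valid only if no day-level variation exists. The second simulation table shows otherwise. Parent-by-meal differences are plausible, since the plan treats meal type as an event characteristic of interest. This stands, and it limits the claim to a likely direction and a range. It does not make M1 adequate: the error rate is then set by two unknown variances.

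2. **No day-of-week test is named.** The sentence speaks of quantifying how fluctuations differ across individuals, Aim 1 is descriptive, and the Power Analysis says there is no formally defined primary end point. That the test is planned is an inference from the general alpha rule and hypothesis 1. This also stands, but intervals for weekday effects from the same model have the same fault.

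3. **Similar is not identical.** The wording leaves room for another random term, and a fuller analysis plan may state one. That is fair, but the equation is printed and the only change named is the covariate.

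4. **A parent-day intercept has a side effect.** The plan uses residuals of these same models to describe between-day fluctuation. With m = 4 the intercept absorbs 4·rho/(1 + 3·rho) of the day effect, taking the parent effect as known: 31% at rho = 0.10, 50% at 0.20 and 63% at 0.30. The variance of day-mean residuals falls to the square of the remainder, about 48%, 25% and 14%. This stands in full and restricts the remedy to inference.

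**Conclusion.** The concern holds in a limited form. As printed, the between-day models have no parent-day component, so tests and intervals for day of week rest on the wrong unit of replication. They are likely anticonservative, because the study's own premise is that practices fluctuate between days, and the article's introduction lists drivers, such as child physical health or lack of planning, that can last a whole day.

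The 6 to 14% (2 reports) and 9 to 36% (4 reports) ranges for the 6-df test are conditional on the assumed rho of 0.05 to 0.30 and on little omitted parent-by-meal variance. Single contrasts are inflated less. If the test were made for each of 4 domains in each of 4 periods, that is 16 tests: 16 × 0.05 = 0.8 false weekday patterns expected at the nominal rate, against 16 × 0.139 = 2.2 at m = 4 and rho = 0.10. The change should be made, but the article does not show that the inflation is severe.

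**What to change.** For inference on any day-level factor (day of week, weekend), do one of the following and state which:
- add a random parent-day intercept, so the model reads D = β0 + β1·Z + β2·X + b_i + d_i(day) + ε;
- use variance clustered at parent-day level or higher;
- analyse parent-day mean scores.

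Report day-of-week tests and intervals only from that analysis. Keep the residual SD, IQR and entropy summaries on a model without the parent-day intercept, or on residuals that retain the day effect, so that the between-day signal is not removed from those metrics.

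The cost is somewhat wider day-of-week intervals and one additional model fit. No new data are needed.

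### No model in the plan has a day level, so the within-day and between-day fluctuation scores both measure total within-person spread

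*Protocol article*

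**What the plan says.** All of this is in the protocol article, Statistical Analysis Plan, Overview.

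- **Model M1.** The domain score for person i at event j is modelled by an intercept, a term in Z, baseline characteristics, a person term b and a residual. Z "is the event characteristic of interest (meal or time period indicator"), and b "is a person-specific random effect, and" there is no other random term. The indices are person and event; there is no day index.
- **Within-day score.** The article states: "within-day consistency across event characteristics (eg, meal type) will be derived by calculating the distribution of SDs of individual residuals from model (M1"). Each person's value is expressed as a z score. The article illustrates it by saying that "an individual whose food parenting practices fluctuate substantially across meals will have a large SD of residuals relative to the population".
- **Between-day score.** Between-day fluctuation "will be quantified using longitudinal mixed models, similar to those described above, with the event characteristics" now standing for factors such as day of the week. Then: "The SD, IQR, and entropy of residuals from these models will also be summarized to characterize between-day fluctuations".
- **Use.** The period-specific models for the child's Healthy Eating Index (HEI) include consistency z "scores that reflect the degree of within- and between-day fluctuations in food parenting practices during that period". Individual domain scores, "as well as consistency and endurance metrics, will be used as inputs to a k-means algorithm"; the resulting clusters are the main predictors in the primary HEI models.

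**The concern.** Events are nested in days and days in persons. A model with only a person effect puts a parent's day-to-day shifts and meal-to-meal shifts into one residual. Exchanging meal for day of the week as the fixed effect changes which population-average pattern is subtracted. It does not change which level of the parent's own variation is left. The two scores carry different labels, but neither isolates the level it is named after.

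Aim 2 names within- and between-day fluctuation as the exposure for child diet. If both scores are total spread, an HEI association cannot be attributed to either kind of fluctuation, entering both brings strong collinearity, and clusters built on them inherit the mislabelling. Aim 1's account of between-day fluctuation would mostly describe within-day spread, unless about half or more of the variation lies between days.

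Two further consequences follow from the same model. Subtracting the average meal pattern removes part of the fluctuation across meals that the score is said to capture. And tests of day-level factors ignore clustering of events within days.

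**Working it through.** **Inputs from the article.** The analytic sample is 200 families, with 4 responses per day over 8 days (Power Analysis): 200 × 8 × 4 = 6400, which matches the article's total. Alpha is 0.05, two-sided. The article gives no correlation or variance split between the two scores, so there is no figure to reproduce.

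**Assumptions (not in the article).** Meal explains 0-40% of score variance and day of week 0-5%. The between-day share of within-person variance is 10-50%. The coefficient of variation (CV) of person-specific SDs is mostly 20-50%. True within-day and between-day SDs are drawn independently. Base case: meal 10%, day of week 3%, day share 30%, CV 35%.

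**Step 1, algebra.** b is constant within a person, so it drops out of that person's residual SD. Let a parent have within-day variance w² and between-day variance s², with m = 4 events on each of 8 days. The expected residual variance is:

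- meal model: w² + s² × m(8−1)/(8m−1) + common day-of-week variance
- day-of-week model: w² + s² × m(8−1)/(8m−1) + common meal variance

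Here m(8−1)/(8m−1) = 28/31 = 0.90. The part that differs between parents, w² + 0.90 s², is the same in both. IQR and entropy are taken on the same residuals and do not separate the levels either.

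**Step 2, simulation** (200 parents, 8 days × 4 events, 60 replicates per setting):

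| Setting (base unless stated) | Correlation of the two scores | Between-day score vs true within-day SD | Between-day score vs true between-day SD |
|---|---|---|---|
| No meal or day-of-week effect | 0.999 | 0.805 | 0.321 |
| Base | 0.975 | 0.791 | 0.322 |
| Meal 20% | 0.957 | 0.778 | 0.315 |
| Meal 30%, day of week 5% | 0.920 | 0.756 | 0.297 |
| Meal 40%, day of week 5% | 0.896 | 0.730 | 0.300 |
| Meal 30%, CV 20% | 0.863 | 0.600 | 0.229 |
| Day share 10% | 0.979 | 0.897 | 0.107 |
| Day share 50% | 0.973 | 0.593 | 0.536 |
| Half of prompts missing | 0.952 | 0.700 | 0.309 |

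A check with REML random-intercept fits gave 0.972 in the base case. When parents also differed in how strongly they follow the average meal pattern, further runs gave correlations from 0.69 to 0.96. At the base correlation the variance inflation from entering both scores is 1/(1 − 0.975²) = 20.

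**Step 3, two opposite parents with the same total variance of 1.** If all variation is within days, the scores are 1.01 (meal model) and 1.05 (day-of-week model). If all variation is between days, they are 0.94 and 0.98. The plan's scores barely separate them. A nested split does: the within-day SD is 0.99 against 0.00, and the SD of day means is 0.48 against 0.97. The 0.48 is event noise averaged over four events, which is why day means need a noise correction.

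**Step 4, the average meal pattern.** Ignore other variation. A parent identical at every meal has M1 residuals equal to minus the centred meal effects, so the score is the SD of those effects. In the base case this is √(0.10/0.87) = 0.34, in units where the typical within-person SD is 1. A parent who swings exactly as the average does has residual 0. The article's example therefore fails for fluctuation that follows the average pattern.

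**Step 5, day-level tests.** The design effect is 1 + (m−1) × day share. With 2 events and a 10% share it is 1.1; with 4 events and a 20% share it is 1.6. The actual size at nominal 5% is 2 × [1 − Φ(1.96/√1.1)] = 6.2% and 2 × [1 − Φ(1.96/√1.6)] = 12.1%.

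**The case against.** The best defence has four parts.

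- **The article condenses a fuller plan.** It speaks of models of this form and similar models, so further random terms might exist elsewhere. This carries some weight for the day-of-week tests. It carries less for the scores, because the article defines them explicitly from these residuals and no step splits a person's residual variance by day.
- **The aims use within- and between-day as one joint phrase.** Hypothesis 4 contrasts consistent and enduring use with inconsistent use, and the only consistency z score constructed explicitly is the within-day one. Total within-person SD is a usable, coarse index of inconsistency. That stands, but it does not justify labelling one score within-day and another between-day. A reader might also infer that all three aims use the scores as exposures. They do not: aim 1 describes fluctuation, and aim 3 models the event-level score and uses the z scores only in exploratory interactions.
- **Adjusting for meal is defensible.** Only shared eating occasions are reported, so meal mix will differ between parents, and an unadjusted SD would partly reflect that mix. This stands. It argues for keeping the adjusted score under an accurate label. The article also computes SD, IQR and entropy of the unadjusted domain scores.
- **The score is not inverted.** From the flat-parent example a reader might infer that the score measures the reverse of what is claimed. In simulations with meal shares of 10-30% and parents varying in how far they follow the meal pattern, the M1 score correlated +0.50 to +0.91 with the raw within-day SD and was never negative. It is contaminated, not reversed.

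**Conclusion.** The point holds as a fault in rules the article states, not as missing detail. The two scores are not literally identical, since they come from two fits, and no single correlation describes them. Their overlap is about 0.97-0.99 with modest meal effects and about 0.7-0.9 when those effects are large or parents differ in following them. The between-day score mainly reflects within-day spread when 10-35% of within-person variance lies between days. At a 50% share it tracks both about equally (0.59 and 0.54) and still isolates neither. All of these sizes rest on assumed variance shares and spreads; the algebra in step 1 does not.

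The consequences fall on aim 2's HEI models, the k-means clusters, and aim 1's description of between-day fluctuation. The excess of false positives in day-of-week tests (about 6-12% at nominal 5%) depends on days clustering to the assumed 10-20%.

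**What to change.** Add a person-by-day random effect, so that events are nested in days and days in persons. Score between-day fluctuation from each person's day effects, or from the SD of day means corrected for event noise. Score within-day fluctuation from the spread of events around the parent's own day mean. A mixed-effects location-scale model with both variances does this in one step and copes with unequal event counts. Keep the meal-adjusted score, label it as departure from the average meal pattern, and report the unadjusted within-day SD beside it.

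In the base case this lowers the correlation between the two scores from 0.975 to 0.32, or to about −0.07 after noise correction. The within-day score then tracks its true SD at 0.92 (0.79 for the M1 score), and the between-day score at 0.57-0.59 (0.32 as written).

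The cost is revised wording and analysis work. No new data are needed, and collection is expected to run to November 2026. The limitation to state is that between-day SDs from 8 days are noisy: with day shares of 10-35% and a 30% spread in true SDs, they correlate only about 0.3-0.55 with the truth.
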